#### **4) C1D21 visit ( $\pm 3$ days)**

- Comprehensive: body weight, vital signs, physical examination;
- Laboratory tests: blood routine, urine routine, stool routine, blood biochemistry, coagulation function, thyroid function and cardiac function;
- 12-ECG;
- Concomitant medications and adverse events were recorded.

### 6.2.2 Cycle 2

Cycle 2 lasts for 21 days, recorded as C2D1 ~ C2D21. Observations and assessments need to be completed during this period for:

#### 1) C2D1 visit

- TQB2858 administration;
- Vital signs and body weight;
- Concomitant medications and adverse events were recorded.

#### 2) C2D21 visit ( $\pm 3$ days)

- Comprehensive: body weight, ECOG score, vital signs, physical examination;
- Laboratory tests: blood routine, urine routine, stool routine, blood biochemistry, coagulation function, thyroid function and cardiac function;
- 12-ECG;
- Record concomitant medication and adverse event;
- Imaging (required for subsequent treatment phase visits):
  - Contrast-enhanced CT/MRI may be performed at the site of target and non-target lesions or other sites that the investigator feels are necessary. The same test method should be used during the screening period;
  - Contrast-enhanced MRI is recommended for head examination. If MRI cannot be performed due to contrast agent allergy or other reasons, contrast-enhanced CT is feasible; if there is no brain metastasis lesion during the screening period, head imaging examination should be performed when there are symptoms of brain metastasis or the investigator considers necessary;
  - Bone scan should be performed for patients with bone metastasis or symptoms of bone metastasis; if there is no bone metastasis during the screening period, bone scan should be performed when there are symptoms of bone metastasis or the investigator considers necessary;
  - Allowed to be completed within 7 days ( $\pm 7$  days) before and after this

visit;

### 6.2.3 Cycle 3 and subsequent singular cycles

#### 1) C (2n + 1) D1 visit

- TQB2858 administration;
- Vital signs and body weight;
- Concomitant medications and adverse events were recorded.

#### 2) C (2n + 1) D21 visit ( $\pm 3$ days)

- Comprehensive: body weight, vital signs, physical examination;
- Laboratory tests: blood routine, urine routine, stool routine, blood biochemistry, coagulation function, thyroid function and cardiac function;
- 12-ECG;
- Concomitant medications and adverse events were recorded.

### 6.2.4 Cycle 4 and Subsequent Even Cycles

Imaging visits: visits will be performed every 2 cycles within 1 year after the start of the study; visits will be performed every 4 cycles if the study duration exceeds 1 year (except for pseudoprogression confirmation and confirmation of PR and CR) until subject's progression out or the end of the study.

#### 1) C (2n + 2) D1 visit

- TQB2858 administration;
- Vital signs and body weight;
- Record concomitant medication and adverse event;

#### 2) C (2n + 2) D21 visit ( $\pm 3$ days)

- Comprehensive: body weight, ECOG score, vital signs, physical examination;
- Laboratory tests: blood routine, urine routine, stool routine, blood biochemistry, coagulation function, thyroid function and cardiac function;
- 12-ECG;
- Record concomitant medication and adverse event;
- Imaging examination;

### 6.2.5 End of Treatment (EOT) Visit

When a subject meet any of the reasons for the end of study treatment, relevant examination procedures for the end of treatment (EOT) visit are required. These tests do not have to be performed at the EOT visit if some of them were done within 7 days before treatment withdrawal. The following tests/procedures should be completed or the following information should be collected at the EOT visit (within 7 days after the end of treatment):

- Comprehensive: body weight, ECOG score, vital signs, physical examination;
- Laboratory tests: blood routine, urine routine, stool routine, blood biochemistry, coagulation function, thyroid function and cardiac function;
- 12-ECG;
- Recording concomitant medication, adverse events and drug recovery;
- Imaging examination (this examination is not required if there is corresponding imaging record due to disease progression);

### 6.2.6 Follow-up Visit

After the end of treatment visit, enter the follow-up period. The safety follow-up period is the interval between the EOT visit and the scheduled follow-up visit, which should occur 30 days ( $\pm 7$  days) after the EOT visit or 30 days ( $\pm 7$  days) after study drug administration if the EOT visit was not performed. Adverse events and SAEs must be reported to at least 30 days after initiation of study drug, the date of the follow-up visit, or until the toxicities resolve, return to baseline, or are deemed irreversible, whichever is longer. Reasonable efforts should be made to have the subject return for the follow-up visit and report all AEs that occur during this period.

If a subject is scheduled to start a new antineoplastic therapy before the end of the safety follow-up period, the safety follow-up visit should be performed before the start of the new antineoplastic therapy. Once new antineoplastic therapy was initiated, subjects entered the survival follow-up period.

After completion of the safety follow-up period, enter into the survival follow-up

period. The first survival follow-up period (including telephone follow-up) occurred 8 weeks ( $\pm 7$  days) after the last safety follow-up and occurred on an 8-week ( $\pm 7$  days) basis until the subject died, lost to follow-up, the study was terminated by the sponsor, or other study closure criteria were met, whichever occurred first. The investigator may follow up the subject, his/her family or the responsible physician by phone to collect whether other anti-tumor treatment was given to the subject before this visit. If other treatments are used, the treatment regimen and cycle number and outcome must be recorded. The patients were followed up until death, and the relevant cause of death and specific time were recorded to obtain overall survival (OS).

For subjects who discontinue study treatment due to intolerance or other reasons, if no radiographic progression is observed, radiographic assessment should still be performed at the original frequency until disease progression or initiation of other anti-tumor therapy (except anti-tumor therapy with traditional Chinese medicine), and radiographic evidence of disease progression should be obtained as much as possible for such subjects.

#### **6.2.7 Unscheduled Visits**

Unscheduled visits may be performed at any time at the discretion of the investigator and appropriate clinical and laboratory tests may be performed based on AEs or other findings.

### **7. Biomarker study**

To explore the expression of CD68, CD163, CD206, IRF8, CD3, CD8, PD-L1, CD20, CD56, B7-H3, CD47 and CD4 in tumor tissues, and to determine the presence of tertiary lymph node structure in tumor tissues based on the positive results in the above tissue sections, 6 white tumor tissue slices (5 microns, for smear and baking gel staining and immunohistochemistry) will be collected from subjects before administration in this study to clarify the characteristics of immunogenic microenvironment of TQB2858 in subjects with advanced high-grade sarcoma.

The collection, numbering, transportation, processing, storage and other detailed

operations of biological samples shall be performed in accordance with the relevant standard operation manual or operating procedures.

## **8. Efficacy evaluation**

TQB2858 injection is a tumor immune drug, and based on the experience of drugs in the same class, the subject may have false progression, i.e. The response assessment criteria for this study were based on RECIST 1.1, while iRECIST criteria were used to confirm response.

Beginning with Cycle 1 Day 1, efficacy will be assessed every 2 cycles over 1 year from the start of the study and every 4 cycles over 1 year until the subject experiences radiologically confirmed disease progression that does not change in frequency due to delay or interruption of treatment. If a subject discontinues study treatment for reasons other than disease progression, tumor imaging assessments at the aforementioned frequency should continue until the subject starts a new antineoplastic therapy, or radiographic evidence of disease progression, or the subject withdraws, or the subject dies, whichever occurs first.

CT or MRI can be used for tumor imaging evaluation at the discretion of the investigator, but the evaluation method, machine and technical parameters should be consistent throughout the study; if there is no contraindication, contrast agent should be used. If imaging has been performed within 28 months (within 3 months for bone scan) before the first dose, and the same method is used in the same center, it can be used as the baseline imaging index. Baseline Imaging examination CT or MRI of the neck, chest, abdomen, and pelvis should be included. Enhanced MRI (recommended) or enhanced CT is required at screening. Imaging should be performed at all suspicious lesion sites. For patients with bone metastasis, bone scan should be used for follow-up of lesions. For patients with bone metastasis, if there is no aggravation of clinical symptoms, each tumor assessment is not required for reexamination. If there is aggravation of clinical symptoms, reexamination should be performed in time. For patients with suspected disease progression before the next scheduled assessment,

unscheduled tumor assessment should be performed. During the trial, only the imaging examination of the lesion site is performed. If there is a suspicious site during the trial, the image of the corresponding site can be additionally examined.

In this study, we preliminarily investigated the therapeutic effect of TQB2858 injection in advanced high-grade sarcoma and assessed the efficacy according to RECIST 1.1 evaluation criteria and iRECIST evaluation criteria. Indicators include objective response rate (ORR), disease control rate (DCR), progression-free survival (PFS), 3-month ORR, overall survival (OS) and duration of response (DOR).

- 1) Objective response rate (ORR): is the proportion of subjects whose tumor volume reduction reaches the prespecified value and maintains the minimum time limit (at the next imaging assessment), including cases of complete response (CR) and partial response (PR);
- 2) Disease control rate (DCR): the proportion of patients whose tumors shrink or remain stable for a certain period of time, including patients with CR, PR and stable disease (SD);
- 3) Progression-free survival (PFS): The time from the first dose to disease progression (PD) or death before PD; if there is no PD or death before PD, the date of the last imaging assessment will be used as the cut-off date;
- 4) Overall survival (OS): The time from the first treatment of a patient to death from any cause.
- 5) DOR: In subjects with CR or PR, the time from the first tumor assessment of CR or PR to PD or death before PD; if a subject with CR or PR did not experience PD or death before PD, the date of the last radiographic assessment will be used as the cut-off date.

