## Notes:

1. Within 28 days after signing the informed consent form, it belongs to the screening period;
2. For details about the out-group visit, see [Chapter 6 for details](#);
3. Safety visit: The safety follow-up period is the interval between the EOT visit and the scheduled follow-up visit, which should occur 30 days (± 7 days) after the EOT visit or 30 days (± 7 days) after study drug administration if the EOT visit was not performed.
4. Survival Visit: The first survival follow-up period (including telephone follow-up) will occur 8 weeks (± 7 days) after the last safety follow-up and occur every 8 weeks (± 7 days) until the subject has died, is lost to follow-up, the sponsor terminates the study, or other study closure criteria are met, whichever occurs first.
5. Height and weight: Height will be measured only during the screening period;
6. Demographics/medical history: Demographic data include date of birth, age, gender, ethnicity and occupation; medical history includes previous treatment regimen, concomitant diseases and treatment, allergy history and smoking history;

7. Vital signs: including body temperature, pulse, respiration and blood pressure;
  8. Physical examination: see [Chapter 6 for details](#);
  9. Infectivity test: hepatitis B virus, HCV and HIV; if HBsAg or HBeAg is positive, HBV DNA test should be performed; if HCV antibody is positive, HCV RNA test should be performed;
  10. Blood routine: See [Table 5 for details](#);
  11. Blood biochemistry: See [Table 5 for details](#);
  12. Thyroid function: See [Table 5 for details](#);
  13. Coagulation function: See [Table 5 for details](#);
  14. Urinalysis: see [Table 5 for details](#);
  15. Stool routine: see [Table 5 for details](#);
  16. Cardiac function: See [Table 5 for details](#);
  17. ECG: If chest pain, palpitation and other symptoms occur, echocardiography, myocardial enzyme spectrum and troponin should be additionally examined;
  18. Imaging examination: see [6.3 for details](#);
  19. Study drug: 3-week treatment cycle, administered on Day 1 of each cycle via intravenous drip, q3w; see details [5.4 Section content](#) ;
  20. Biomarkers: see [Chapter 7 for details](#) ;
- Check window period: the time window allowed for the visit on the specified visit day. If the specific item has the time window requirement, implement it according to the specific item requirement

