### **2.4 Primary Endpoints**

- ORR based on RECIST 1.1 and iRECIST;

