## **4. Subject Selection and Withdrawal**

### **4.1 Inclusion criteria of subjects**

Patients who meet all of the following inclusion criteria can be included in this trial:

- 1) Histologically confirmed unresectable, recurrent, or metastatic high-grade sarcoma;
- 2) Patients who previously received at least one line of treatment, with disease progression or intolerance during treatment, or disease progression after the end of treatment; (except for alveolar soft part sarcoma and clear cell sarcoma)
  - a) Cohort 1: Primary alveolar soft part sarcoma;
  - b) Cohort 2: alveolar soft part sarcoma failing PD-1 therapy;
  - c) Cohort 3: Other subtypes (pleomorphic sarcoma, classic osteosarcoma, Ewing sarcoma, chondrosarcoma, dedifferentiated liposarcoma, etc.)
- 3) Age: 18-70 years old;
- 4) ECOG score: 0 ~ 1;
- 5) Life expectancy of more than 3 months;
- 6) Normal function of major organs meeting the following criteria:
  - a) Hematology (not transfused and not receiving growth factor support before screening): hemoglobin (HGB)  $\geq 80$  g/L; neutrophil count (NEUT)  $\geq 1.5 \times 10^9$ /L; platelet count (PLT)  $\geq 90 \times 10^9$ /L;
  - b) Biochemistry: alanine aminotransferase (ALT) and aspartate aminotransferase (AST)  $\leq 2.5 \times$  ULN (ALT and AST  $\leq 5 \times$  ULN for patients with primary hepatobiliary tumors or liver metastases); total bilirubin (TBIL)  $\leq 1.5 \times$  ULN

- (TBIL  $\leq 3 \times$  ULN for patients with Gilbert's syndrome); creatinine (CRE)  $\leq 1.5 \times$  ULN or creatinine clearance  $\geq 60$  ml/min;
- c) Coagulation function: activated partial thromboplastin time (APTT), international normalized ratio (INR), prothrombin time (PT)  $\leq 1.5 \times$  ULN;
- d) Left ventricular ejection fraction (LVEF)  $\geq 50\%$ ;
- 7) Female patients of childbearing potential must have a negative serum or urine HCG test within 7 days prior to enrollment and must be non-lactating; patients should agree to take contraceptive measures during the study and within 6 months after the end of the study period;
- 8) The patient voluntarily joined the study, signed the informed consent form, and had good compliance.

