## 6. Test Flow

### 6.1 Screening Visit

The screening period is from 28 days before the first dose to 1 day before the first dose, recorded as D-28 ~ D-1. Observations and assessments need to be completed during the screening period for:

- 1) Signed informed consent (completed prior to items 2-12 below and prior imaging studies may be completed prior to signing informed consent);
- 3) Pathological reports, disease stages, and molecular characteristics of the disease were collected for the diagnosis of advanced high-grade sarcoma. D-28 to D-1 done;
- 4) Tissue sections or biopsies were collected for PD-L1, TGF- $\beta$  and other expression detection (for details, see Fig. 7.4 Section ). D-28 to D-1 done;
- 5) Demographic data: date of birth, age, gender, ethnicity, occupation. D-28 to D-1 done;
- 6) Medical history Treatment history (completed on D-28 ~ D-1): previous treatment regimen (surgery, chemotherapy, radiotherapy, targeted therapy, other anti-tumor therapy), previous major diseases, concomitant diseases and treatment allergy history, smoking history;
- 7) Concomitant medications and adverse events were recorded. D-28 to D-1 done;

- 8) Imaging examination (completed on D-28 ~ D-1):
- Contrast-enhanced CT/MRI (the examination sites include: neck, chest, abdomen, pelvic cavity or other differential examinations which may include the above areas, as well as the suspected lesion sites);
  - Contrast-enhanced MRI is recommended for head examination. If MRI cannot be performed due to contrast agent allergy or other reasons, contrast-enhanced CT is feasible;
  - Patients with bone metastasis or symptoms of bone metastasis should receive bone scan;
  - If imaging has been performed within 28 months (within 3 months for bone scan) before the first dose, and the same method is used in the same center, it can be used as the baseline imaging index.
- 9) Overall response (D-7 ~ D-1 completed, the subsequent visits of specific items are the same and not listed in detail any more):
- Height, weight, ECOG score;
  - Vital signs: body temperature, pulse, respiration and blood pressure;
  - Physical examination: examination of various tissues and organs (skin, mucosa, lymph nodes, head, neck, chest, abdomen, spine/limbs, nervous system, etc.);
- 10) 12-Lead ECG, echocardiography: Echocardiography should include score (LVEF). Completion of D-7 ~ D-1;

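### The baseline-imaging exception in Sections 6.1 and 8 allows a CT/MRI up to 28 months old and contradicts the protocol's own 28-day screening window; the unit is probably wrong

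*Protocol*

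**What the plan says.** Section 6.1 defines screening: "The screening period is from 28 days before the first dose to 1 day before the first dose". Item 8 of that section opens with the matching window for scans: "Imaging examination (completed on D-28 ~ D-1". The last bullet of the same item then makes an exception: "If imaging has been performed within 28 months (within 3 months for bone scan) before the first dose". Provided the same method was used in the same centre, "it can be used as the baseline imaging index". Section 8 repeats the exception in the same terms.

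Three other places bear on it:

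- Note 1 to the visit schedule also gives a 28-day screening period, counted from consent: "Within 28 days after signing the informed consent form, it belongs to the screening period". The schedule marks imaging at screening.
- Item 1 of Section 6.1 accepts scans taken before consent, with no age limit of its own: "prior imaging studies may be completed prior to signing informed consent".
- The primary endpoint in Section 2.4 is "ORR based on RECIST 1.1 and iRECIST".

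**The concern.** The two imaging sections state a limit that cannot be squared with the window heading one of them. The exception for CT/MRI, which measures the target lesions, is also looser than the exception for bone scan.

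The baseline scan is the reference for the RECIST categories. Section 4.1 requires, for most patients outside alveolar soft part and clear cell sarcoma, earlier treatment and a reason for having left it: "Patients who previously received at least one line of treatment, with disease progression or intolerance during treatment, or disease progression after the end of treatment". Section 4.2 (exclusion 2a) sets a 4-week washout from earlier anticancer therapy. A baseline taken in the 28 days before dosing therefore generally follows the last prior therapy. A scan up to 28 months old carries no such assurance. It could predate a treatment line, a resection, or the progression that made the patient eligible.

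Tumour change before the first dose could then be attributed to TQB2858 in either direction. ORR and DCR could be misstated. PFS could be shortened, since Section 8 times it from the first dose while the tumour reference would lie far earlier. DOR is exposed less directly: its clock starts at the first CR or PR, but the set of responders it is computed on could be wrong. RECIST 1.1 progression is also a ground for stopping treatment in Section 4.3.2, although Section 4.7 allows continuation in some cases.

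**Working it through.** **1. Size of the contradiction.** Inputs: 28 months and 3 months (Sections 6.1 item 8 and 8); 28 days (Section 6.1 and visit schedule note 1).

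- 28 × 365.25 / 12 = 852 days, or 2.33 years.
- 852 / 28 = 30.4 times the screening window.
- 28 / 3 = 9.3 times the bone-scan limit.
- 852 − 28 = 824 days of extra age allowed.

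**2. Does anything withdraw the exception?** Section 8 goes on to say that enhanced MRI (recommended) or enhanced CT is required at screening. That mirrors the head-imaging bullet in Section 6.1, where MRI is recommended for the head with CT as fallback. It does not clearly require a new scan of the body lesions. No other text limits the age of the CT/MRI or calls for a repeat when an old scan is used.

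**3. Effect on one subject.** Let r be the sum of diameters at first dose divided by the sum on the old scan. The thresholds are taken as a 30% decrease for PR and a 20% increase for PD. The protocol invokes RECIST 1.1 without restating them. With no change at all on treatment, the apparent change is r − 1. The true shrinkage after first dose needed to be called PR is 1 − 0.7/r.

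| r | Apparent change with no drug effect | Category | True shrinkage needed for PR |
|---|---|---|---|
| 0.7 | −30% | PR | 0% |
| 1.0 | 0% | SD | 30% |
| 1.2 | +20% | PD | 41.7% |
| 1.3 | +30% | PD | 46.2% |
| 1.5 | +50% | PD | 53.3% |

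The PD entries apply at the first on-study scan, where the baseline is the comparator; later scans may be compared with a smaller on-study sum. Section 8 requires a response to be maintained at the next imaging assessment. That does not remove a false PR, because the next scan is compared with the same old baseline.

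**4. How easily could r reach 1.2?** This rests on an assumption that is not in the documents: a volume doubling time d of 90 to 180 days. Diameter growth over 180 days is 2^(180/(3d)).

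- d = 90: 2^(0.667) = 1.59, growth of 59%.
- d = 180: 2^(0.333) = 1.26, growth of 26%.

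These percentages are relative to the old scan, which is also how the 20% threshold is measured at the first on-study assessment. Relative to the true diameter at dosing, the old scan is too small by 1 − 1/1.26 = 21% to 1 − 1/1.59 = 37%.

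**5. Effect on a cohort.** The minimum cohort size in Section 11.2 is 10. One misclassified subject moves ORR by 1/10 = 10 percentage points. Exact 95% intervals are 0% to 31% for 0/10 and 0.3% to 45% for 1/10.

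**The case against.** The strongest reply is that this is a plain slip which no site would act on. The number 28 matches the screening window, and months makes no sense beside a 3-month limit for bone scan. The document also has a similar slip in Section 5.5.4, where a post-treatment period is given as 28 mg in one row and 28 days in the row before. The screening window is clear, the schedule already calls for imaging at screening, and the exception is permissive and confined to the same method and centre.

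Most of that stands. It makes a unit error the best explanation and actual use of a two-year-old scan unlikely. It does not remove the contradiction. The wording appears in both operative imaging sections and survived version 1.1, which was partly an erratum. A site using it would not be deviating from the protocol. Nor can a reader dismiss an exception merely because it exceeds the window, since the 3-month bone-scan allowance does exactly that.

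It is also fair to object that the growth figures are assumed. One constant rate cannot describe histologies from alveolar soft part sarcoma to Ewing sarcoma and osteosarcoma. The figures show only that a few months can be enough to matter.

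Two stronger readings should be resisted. A reader might infer that the sponsor chose to accept very old baselines; the stated window and the bone-scan limit speak against that. A reader might also infer that ORR is biased. The documents do not show how many subjects, if any, had an old baseline, so no bias in the trial's result can be stated.

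**Conclusion.** The point holds as an internal contradiction, probably a unit error, in a rule that defines the reference measurement for the primary endpoint. The size of the discrepancy, 852 days against 28, is certain. The effect on ORR, DCR, PFS and the responder set for DOR is possible, can go in either direction, and cannot be quantified without knowing how many subjects used an older scan. The 26% to 59% growth illustration depends wholly on the assumed doubling times; the contradiction does not. The point deserves correction despite its likely innocence, because cohorts may be as small as 10, there is no control arm, and one wrong baseline can change the estimate materially.

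**What to change.** Change months to days for CT/MRI in the last bullet of Section 6.1 item 8 and in the matching sentence of Section 8, so that the exception agrees with the window from 28 days to 1 day before the first dose. The sentence then still has a purpose: it lets a recent scan taken before consent serve as baseline.

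If any subject has already been enrolled with an older baseline CT/MRI, list the interval from scan to first dose and report ORR with and without those subjects. The protocol has no such comparison at present; it would be an addition, needed only if such subjects exist.

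The cost is one word in two places. A subject who would have relied on an older scan needs the screening scan that the visit schedule already includes.

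### Sections 6.2.2 and 8 conflict on repeat bone scans, and scheduled follow-up imaging is confined to known lesion sites, so progression can be found late and PFS and DOR may be overstated

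*Protocol*

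**What the plan says.** **Baseline field.** Section 6.1, item 8, sets out contrast-enhanced CT/MRI: "the examination sites include: neck, chest, abdomen, pelvic cavity", together with suspected lesion sites. Section 8 agrees: "Baseline Imaging examination CT or MRI of the neck, chest, abdomen, and pelvis should be included".

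**On-study field.** Section 8 states: "During the trial, only the imaging examination of the lesion site is performed". It continues: "If there is a suspicious site during the trial, the image of the corresponding site can be additionally examined". Section 6.2.2 (C2D21 visit) is similar: "Contrast-enhanced CT/MRI may be performed at the site of target and non-target lesions or other sites that the investigator feels are necessary". Under 6.2.2, a subject with no brain or bone metastasis at screening has head imaging or a bone scan only for symptoms or on the investigator's judgement.

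**Bone metastasis.** Section 6.2.2 says: "Bone scan should be performed for patients with bone metastasis or symptoms of bone metastasis". Its imaging list is marked as applying to later treatment-phase visits too. Section 8 first names bone scan as the means of following bone lesions, and then says: "For patients with bone metastasis, if there is no aggravation of clinical symptoms, each tumor assessment is not required for reexamination".

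**Cross-reference.** Footnote 18 of the visit schedule sends the reader to Section 6.3 for imaging. Section 6 ends at 6.2.7.

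**Endpoints affected.** ORR is primary (Section 2.4); PFS and DOR are secondary (Section 2.5). By Section 8, PFS and DOR end at progression or death and are otherwise cut off at the last imaging assessment.

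**The concern.** Progression can be recorded on schedule only if the scheduled scan looks where it occurs. Here a region that was clear at baseline need not be imaged again until someone suspects it. Known bone metastases are re-examined at each assessment under one section and only on worsening symptoms under the other. Two sites could follow the same kind of subject differently and both comply.

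The error runs one way. Progression found late lengthens PFS and DOR. Progression never found leaves the subject censored at the last scan. A partial response at the known lesions can stand although a new lesion exists elsewhere. The trial is single-arm, so no concurrent arm shares the bias. Scan coverage is a site procedure, so no later analysis can recover images that were not taken.

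**Working it through.** The protocol states no figure on this point and plans no hypothesis test (Section 11.3.2), so there is nothing to reproduce. The check compares the text and then illustrates the size.

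**1. Text comparison**

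| Item | Section 6.2.2 | Section 8 |
|---|---|---|
| Bone scan, bone metastasis present | Required at imaging visits, with no worsening condition | Not required at each assessment unless symptoms worsen |
| Regions clear at baseline | Investigator's discretion | Only if a site is suspicious |
| Target and non-target lesion sites | CT/MRI | Lesion site imaged |

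The first row is a contradiction. In the second row the sections broadly agree, and neither requires scheduled re-imaging of a clear region. The visit schedule resolves neither row, because its reference leads nowhere.

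**2. Illustration for PFS**

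Inputs from the protocol:
- Assessment every 2 cycles in year 1 (2 × 3 = 6 weeks), then every 4 cycles (4 × 3 = 12 weeks).
- Median PFS of 18 weeks, as Section 1.1 reports for the soft tissue sarcoma cohort of the cited pembrolizumab trial.

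Assumptions not in the protocol:
- Progression times are exponential.
- A new lesion counts as progression under the named response criteria, whose rules the protocol does not print.
- A share q of progressions, 10-30%, is recorded one or two visits late.

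The true progression-free share is S(t) = 2^(−t/18). So S(6) = 0.794, S(12) = 0.630, S(18) = 0.500 and S(24) = 0.397.

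- One visit late: recorded share = S(t) + q × [S(t − 6) − S(t)]
- Two visits late: recorded share = S(t) + q × [S(t − 12) − S(t)]

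For t = 18, one visit late:
- q = 10%: 0.500 + 0.1 × (0.630 − 0.500) = 0.513
- q = 30%: 0.500 + 0.3 × 0.130 = 0.539

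| Week | No delay | One visit late, q = 10-30% | Two visits late, q = 10-30% |
|---|---|---|---|
| 12 | 63.0% | 64.6-67.9% | 66.7-74.1% |
| 18 | 50.0% | 51.3-53.9% | 52.9-58.8% |
| 24 | 39.7% | 40.7-42.8% | 42.0-46.7% |

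A simulation on the same inputs, with 12-week visits after week 54, gives a mean recorded PFS of 29.5 weeks without delay, 30.2-31.6 weeks one visit late and 30.9-33.7 weeks two visits late. DOR moves in the same direction because it ends at the same event.

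**3. Illustration for ORR**

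Assume that a share f of apparent responders has an unseen new lesion. The true ORR is then the apparent ORR × (1 − f). With the cited 18%:
- f = 5%: 18% × 0.95 = 17.1%
- f = 20%: 18% × 0.80 = 14.4%

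One misclassified subject changes ORR by 1/10 = 10 points in a cohort of 10 and by 1/30 = 3.3 points in a cohort of 30. That is arithmetic for any single error and does not show that one is likely. For scale, the exact 95% CI for 7/40 (17.5%) is 7.3-32.8%.

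**The case against.** The best defence is that the protocol has safeguards. The investigator may image any other site thought necessary. Suspected progression calls for an unscheduled assessment. A physical examination recurs at each day-21 visit. Efficacy is described as preliminary, nothing is tested, and PFS and DOR are secondary. Lesion-site imaging is stated in both sections, so it is a disclosed choice.

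Much of this stands. It limits the claim to lesions that can be missed or found late and endpoints that may be overstated. But every safeguard starts from suspicion or judgement, so none secures detection of an asymptomatic new lesion. The requirement that a response hold at the next imaging assessment does not help if that assessment uses the same field. The bone-scan contradiction is untouched.

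A reader might infer four stronger things that the documents do not support:

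- **That Cohort 3 bone sarcomas as such are followed under two rules.** The conflicting sentences concern bone metastasis, in any cohort. A primary bone tumour is a lesion site and is imaged under 6.2.2.
- **That skipping a bone scan makes the overall response not evaluable.** Section 6.2.2 provides CT/MRI at target and non-target sites, and Section 8 does not forbid a scan. No part of the protocol states that consequence, and a subject who was not evaluable would not raise ORR.
- **That each late event is delayed by at least one interval.** An unscheduled assessment can shorten the delay.
- **That ORR is materially inflated.** The illustrated shift is small beside the exact interval.

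**Conclusion.** The point holds in two parts. The conflict between Sections 6.2.2 and 8 on repeat bone scans is certain from the text. The limited follow-up field is also plain, and its consequence is a risk: asymptomatic new lesions or bone progression can be missed or found late. The bias is upward, mainly in PFS and DOR and less in ORR.

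The size cannot be derived from the protocol. If 10-30% of progressions are recorded one visit late, 18-week PFS rises by 1.3 to 3.9 points (from 50.0% to 51.3-53.9%); at two visits late it rises by 2.9 to 8.8 points. These figures rest on the assumed shares and delays, an exponential model and a median borrowed from another drug's trial. The change should be made because it is cheap and the lost images cannot be recovered later.

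**What to change.** - Reconcile Sections 6.2.2 and 8 to one bone-imaging rule for endpoint assessment. It should apply equally to all subjects at every scheduled assessment and not depend on symptoms, so that every lesion recorded at baseline is re-imaged by the same method.
- Replace the sentence restricting imaging to the lesion site with one fixed anatomical field for all scheduled assessments, chosen from the regions already imaged at baseline. Any baseline region left out keeps the present gap, so the choice should be explicit. Investigator-requested extra sites and unscheduled assessments can stay as additions.
- Correct footnote 18 of the visit schedule so that it points to the section holding the imaging rules.

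The cost is mainly wording. Some subjects would have a longer scan field in the same session. If the Section 6.2.2 schedule is the one kept, subjects with bone metastasis would have repeat bone scans that Section 8 now lets sites omit.
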